**Day 9**

- The dressings on the wound are removed
- Case Report Forms (CRFs) (Appendix 5) completed by clinician which includes:
  - Clinical exam
  - Evaluation of patient pain level
  - Occurrence of any adverse events
  - Current Medications
  - Photograph of the penis taken if consent granted
  - Reminders to abstain from sexual intercourse

**Day 14**

- Client Interviews
- Case Report Forms (CRFs) (Appendix 5) completed by clinician which includes:
  - Clinical exam
  - Evaluation of patient pain level
  - Occurrence of any adverse events
  - Current Medications
  - Photograph of the penis taken if consent granted
  - Reminders to abstain from sexual intercourse
  - Assessment of wound healing

**Day 21, Day 28, Day 35, Day 42, Day 49, Day 56, Day 63, Day 90**

Patients will be followed in weekly visits until Day49 or until determined fully healed by a clinician (whichever is later). Visits will also occur on Day 90 for those men participating in the psychosocial questionnaire. In each follow-up visit other than Day 90, the following will occur:

- Case Report Forms (CRFs) (Appendix 5) completed by clinician which includes:
  - Clinical exam
  - Evaluation of patient pain level
  - Occurrence of any adverse events
  - Current Medications
  - Photograph of the penis taken if consent granted
  - Reminders to abstain from sexual intercourse until fully healed
  - Assessment of wound healing

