**The Primary Objectives are**:

- 1. To assess the safety of the PrePex™ device when applied to HIV positive men by assessing the rate of the clinical adverse events.

1. **The Secondary Objectives are:**
   1. To assess the level of care required to provide PrePex™ MC to HIV positive men, when taking into account the following parameters:
      1. PrePex™ procedure duration (a combination of the application and removal procedure times)
      2. Pain management at different stages of the procedure
      3. Time to complete healing, defined as, intact epithelium (unbroken skin) covering the epithelial as judged by the provider on visual inspection, meaning that none of the following are present: sutures, scabbing, drainage, moisture, gaps between epithelial edges or ulceration.]
   2. To evaluate the acceptability of the PrePex™ procedure to HIV-positive men as well as service providers.
   3. To evaluate Facilitators/Barriers for seeking VMMC among HIV-infected men
   4. To assess compliance with instructions to refrain from sexual intercourse until seven weeks post-placement-- Day 49 post-placement visit (6 weeks post-removal) or as instructed by a clinician, whichever is later, as a public health safety issue.
   5. Assess AE monitoring and reporting systems with respect to completeness and timeliness of reporting

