**B. RESEARCH PROCEDURES INVOLVED.**

1. Provide a complete description of: a. the study design, and b. sequence and timing of all study procedures that will be performed, e.g., volume of blood, size of biopsy, drug administration, questionnaire, name of psychological test. Provide this information for each phase of the study (pilot, screening, intervention and follow-up). **Use lay language**. Attach study flow sheet, if available.

- - 1. **Study Design**

This is a one arm, open label, prospective cohort study to assess the safety and acceptability of PrePex™ device circumcision when performed by trained PrePex™ MC Providers in a HIV infected male population. The study will involve 400 HIV+ men. The estimated study timeline of 18 months is:

| **Month** | **1** | **2** | **3** | **4** | **5** | **6** | **7** | **8** | **9** | **10** | **11** | **12** | **13** | **14** | **15** | **16** | **17** | **18** |
| --- | --- | --- | --- | --- | --- | --- | --- | --- | --- | --- | --- | --- | --- | --- | --- | --- | --- | --- |
| **Study Phase** | **Start-up** | | | **Recruitment** | | | | | | **Patient Follow-Up** | | | **Analysis and Report Writing** | | | | | |

The study will have two study components which will be concurrently implemented in an estimated period of 12-18 months. Clinicians and staff involved in the study will follow the standard operating procedures of the study (SOP): Appendix 3.

1. Clinical Component

PrePex™ devices will be applied and removed by trained operators (nurses/doctors) and participants will be followed up over multiple review visits (Procedures and Schedule) to collect data on the clinical adverse events, pain, and time to complete healing. We will compare the rates of AEs among HIV+ men with PrePex MC to the lower historical proportion of men who experience an AE with surgical MC of 2.0% as seen in Kenya [[22](#_ENREF_22)] and not to the higher rates of AEs of around 3% as seen in both Uganda [[23](#_ENREF_23)] and South Africa [[24](#_ENREF_24)]. Additionally, we will qualitatively compare this data to those collected in Zimbabwe from two previous studies and routine surveillance in Zimbabwe: 1. a comparison group of HIV-uninfected men who were recently circumcised by the same MC providers using the PrePex device; 2. a comparison group of HIV-uninfected men who recently underwent routine VMMC by MC providers using the forceps-guided method.

1. Psychosocial Component

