Individual interviews will be conducted by trained psychosocial interviewers to collect data from HIV-infected participants on satisfaction with the PrePex™ MC procedure, attitudes towards MC, compliance with instructions to refrain from sexual intercourse for 7 weeks post placement [(Day 49 or 6 weeks post removal) or until a clinician tells them that they are fully healed – whichever is later], barriers and motivators to uptake of VMMC through PrePex™, opinions around convenience of the device, tolerance of potential odour and whether participants would recommend PrePex™ MC to others. The interviews with same participants will be held at three points in time: prior to the procedure, two weeks post-procedure, and 90 days post-procedure (Appendices 6-8). In addition all health care providers at facilities where PrePex™ circumcision is offered will be interviewed on the acceptability of the PrePex™ procedure for HIV-infected clients. Interviews with providers (Appendix 9) will take place at one time point approximately 4 weeks post study initiation.

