c. Ethnic and racial minority populations: We anticipate the ethnic and racial distribution of the study population will reflect the ethnic and racial distribution of men willing to participate in the VMMC program in the areas in Zimbabwe we are working in.

3. What characteristics (inclusion criteria) must subjects have to be in this study? (Answer for each subject group, if different.)

Inclusion Criteria:

- Agrees to take an HIV test
- HIV sero-positive
- WHO HIV clinical stage 1 or 2
- Age 18 years and above
- Agrees to be circumcised by PrePex™
- Able to understand the study procedures and requirements
- Completes VMMC counseling
- Agrees to return to the health care facility for follow-up visits (or as instructed) after his circumcision until complete healing 7 weeks from device application (Day 49 visit) or until cleared by a clinician, whichever is later
- Able to comprehend and freely give informed consent for participation in this study

4. What characteristics (exclusion criteria) would exclude subjects who are otherwise eligible from this study? (Answer for each subject group, if different.)

Exclusion Criteria:

- Known bleeding/coagulation abnormality (excessive bleeding from nosebleeds, pulled tooth, or gums)
- Uncontrolled diabetes (frequent treatment in a clinic or recent hospitalization for diabetes, frequent infections, hypertension, or kidney disease),
- Active genital infection, anatomic abnormality or any other condition, which in the opinion of the investigator prevents the subject from undergoing circumcision using PrePex.
- HIV sero-negative
- HIV status unknown
- WHO HIV stage 3 and above
- Latex allergy
- Does not agree to PrePex

5. Describe the subject recruitment strategies you will use for each group of subjects. (Attach advertisements, flyers, contact letters, telephone contact protocols, Health Sciences recruitment web site template, etc.)

Study staff may identify potential participants from any of the following sites: OI and VCT centres, Zengeza clinic, Chitungwiza hospital, and OI clinics at Beatrice and Wilkins hospitals. After learning about the study, those who agree to be circumcised using PrePex will be requested to visit Zengeza clinic for further screening by the study coordinator using eligibility criteria before actual recruitment into the study. Services at the study site, Zengeza clinic, will be offered every day from 8:00 am to 4:00 pm except on Sunday.

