**E. RISKS AND BENEFITS**

1. Describe nature and degree of risk of possible injury, stress, discomfort, invasion of privacy, and other side effects from all study procedures, drugs and devices (standard and experimental), interviews and questionnaires. Include psycho-social risks as well as physiological risks. Include risks of withholding standard care or procedures if this is the case. Do not reference the consent form.

There is potential increased risk of male to female HIV transmission during the period of wound healing. Participants will be repeatedly advised to abstain from any sexual activity before complete wound healing. Patients will be reminded at each visit that abstinence is the safest way to avoid transmission and support wound healing. However, if the man cannot abstain, condoms should always be used or other forms of sexual intimacy should be practiced until the wound is fully healed.

As a routine medical preventive procedure, MC via PrePex includes standard risks which are minimized and managed via standard care and follow-up; any additional MC-related risk that may be incurred by participants by virtue of their HIV status will be monitored closely and managed as described above. There are other minimal risks of participating in this study such as feeling of discomfort or little pain due to needle prick to collect blood for CD4 counts. Participants will also be informed that they can withdraw from the study at any time with no repercussions.

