**F. ADVERSE EVENTS OR EFFECTS**

1. Who will handle adverse events?  Investigator  Referral  Other, explain:

The participant will be instructed to return to the study site or the nearest hospital (in the case of dislodgement or severe pain) in case of any unexpected event, for example if there is severe discoloration of the penis, signs of infection (purulence), severe or increasing pain, if any part of the device moves for any reason, if the distal part of the foreskin detaches, or any other significant concern that they may have. The participant will be reminded to abstain from sex and to avoid masturbation until 7 weeks post placement or until told that they are fully healed by a clinician, whichever is later. Clients will be instructed that if the device becomes displaced (moves) for any reason that he must seek medical care at a hospital immediately, and that if the device components become displaced and the client doesn’t return immediately for care, there is a risk of permanent damage to his penis.

In the event of a complication meeting the case definition for a clinical AE, the provider will document the complication in the register according to the guidelines. Mild post-operative infections will be managed with wound cleansing and dressing, and antibiotics will be prescribed (see medications list) where clinically indicated. If device components become displaced, a surgical circumcision may be required.

If complications or delayed healing require longer follow-up, men will be followed by study staff as long as necessary or until study close-out. If clinical care is required after study close-out, care will be provided at the study site as part of regular clinical service. If necessary, men may be referred to a hospital near the study site for additional care.

2. Are your facilities and equipment adequate to handle possible adverse events? Yes  No, explain:

3. Who will be financially responsible for treatment of any **medical problems or physical side effects** that appear to be caused by the study**,** including any effects of a blood draw (such as a local infection)?

Not applicable; there are no risks of medical problems or physical side effects.

Department of Defense (DoD) or a DoD component (for example, the Navy).

*Select this box if there are possible medical problems or physical side effects* ***and*** *the research is directly funded by the DoD or a DoD component.*

The VA (Veterans Affairs)

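### The abstinence reminder for the Day 21 to Day 42 visits leaves out the Day 49 minimum against which compliance is judged

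*Protocol*

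**What the plan says.** Three places in the protocol set a floor at Day 49.

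- Secondary Objectives (Section IX): men are to refrain from intercourse "until seven weeks post-placement-- Day 49 post-placement visit (6 weeks post-removal) or as instructed by a clinician, whichever is later". The overview table under Data Collection labels compliance with instructions as objective 1.2.4, assessed by interview in 103 men.
- Section B.1, Psychosocial Component: the interviews ask about compliance with the same rule, "Day 49 or 6 weeks post removal) or until a clinician tells them that they are fully healed – whichever is later".
- Section F.1: men are to be reminded to abstain "until 7 weeks post placement or until told that they are fully healed by a clinician, whichever is later".

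Two places mention healing alone.

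- Section B.1, the checklist headed Day 21 to Day 90: "Reminders to abstain from sexual intercourse until fully healed".
- Section E.1: "Participants will be repeatedly advised to abstain from any sexual activity before complete wound healing". The fallback advice there, on condoms or other forms of intimacy, also runs only to full healing.

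The later-of rule does appear in that same checklist section, but only for how long weekly visits continue: "until Day49 or until determined fully healed by a clinician (whichever is later". The inclusion criteria (Section D.3) use it in the same way, for the follow-up a man agrees to: "until complete healing 7 weeks from device application (Day 49 visit) or until cleared by a clinician, whichever is later".

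**The concern.** Compliance can be judged only against the instruction that was given. Objective 1.2.4 uses a rule with a fixed minimum of seven weeks. The reminder listed for the later clinic visits has no such minimum. Where the two part, a man can do exactly what his visit reminder said and still fall short of the rule he is scored against. The compliance proportion would then mix men who ignored the advice with men who followed a shorter version of it. The objective presents compliance as a matter of public health safety, so the result should be interpretable.

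**Working it through.** **The plan's own figure.** Seven weeks from placement is 7 × 7 = 49 days. Removal is on Day 7, and 49 − 7 = 42 days = 6 weeks. So Day 49, seven weeks after placement and six weeks after removal agree with one another, and the floor itself is sound.

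**The two rules.** Let H be the day on which a clinician certifies full healing.

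- Objectives, Psychosocial Component and Section F.1: abstain until max(49, H).
- Checklist bullet, read literally: abstain until H.
- Difference: max(49, H) − H, which is 49 − H when H is before Day 49 and zero otherwise.

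| Certified healed at | Checklist end point | Section F.1 end point | Gap |
|---|---|---|---|
| Day 21 | Day 21 | Day 49 | 49 − 21 = 28 days |
| Day 28 | Day 28 | Day 49 | 49 − 28 = 21 days |
| Day 35 | Day 35 | Day 49 | 49 − 35 = 14 days |
| Day 42 | Day 42 | Day 49 | 49 − 42 = 7 days |
| Day 49 or later | H | H | 0 |

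The checklist reminder applies at seven visits (Days 21, 28, 35, 42, 49, 56 and 63). The wordings give different end points only for certification at the first four.

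**Does the objective's clinician clause close the gap?** No. It adds the clinician's instruction to Day 49 and takes the later of the two, so early clearance cannot move the end point before Day 49.

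**Are other reminders in conflict?** No. The Day 7, Day 9 and Day 14 lists and the adverse-event text in Section E.2 tell men to abstain without naming an end point.

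**Effect on the estimate.** One man classified differently moves the compliance proportion by 1/103 = 0.97 percentage points, and by more if fewer than 103 are interviewed, since that number is a maximum. This is the size of one step, not an estimate of bias. The protocol gives no healing distribution for PrePex in HIV-positive men and no figure for how many would resume sex inside the gap.

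**The case against.** The best defence is that the rule is already clear. Section F.1 writes out the full reminder, and two other places agree with it. The checklist bullet is one line in a list of form contents, which staff would naturally read as shorthand. The list also applies at every visit other than Day 90, and visits run at least to Day 49, so a man certified at Day 28 is still due a reminder on Days 35, 42 and 49. That sits badly with the idea that abstinence ends at certification. All of this supports Day 49 as the intended minimum.

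It does not remove the inconsistency. The bullet names an end point, and it is a different one. A man already told he is healed has met that condition, so repeating the bullet's words at later visits asks nothing more of him.

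Section E.1 is weaker evidence. It forbids sexual activity during healing and does not say when it may resume, so its fault is omission.

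It is also fair to say that a man who resumes before Day 49 is correctly non-compliant under objective 1.2.4 as written. The difficulty is in interpreting that result if he was told something shorter.

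A reader might go further and infer that men will in fact be told the shorter rule. The document cannot show this: study staff "will follow the standard operating procedures of the study (SOP): Appendix 3", and that appendix, the consent form and the questionnaires are not shown.

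A reader might also infer added risk to partners. That is not supported. Every version advises abstinence before healing, and the trial summarised under Risks for their partners (Section A) found no difference in HIV incidence when couples waited until the wound had healed.

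**Conclusion.** The point holds as a minor internal contradiction. The checklist reminder states an end point without the Day 49 minimum, and the Section E.1 advice omits that minimum too. The gap is 28, 21, 14 or 7 days for a man certified healed at Day 21, 28, 35 or 42, and nothing from Day 49 on.

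Any practical effect needs four things together: the man is among the up to 103 interviewed, he is certified by Day 42, staff gave him the checklist wording, and he resumes sex before Day 49. The number of such men is unknown, and it is zero if staff use the Section F.1 wording. The textual difference is certain; its effect is not. It would be wrong to read the checklist as permission to resume at healing, or to claim material bias. Only one secondary objective is touched, and the primary safety endpoint is unaffected.

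**What to change.** Reword the checklist bullet for Day 21 onward so that it carries the Section F.1 end point: remind the participant to abstain until Day 49 or until a clinician tells him he is fully healed, whichever comes later. Bring the abstinence advice in Section E.1 into line with it. No other reminder needs to change. The cost is an edit to one bullet and one short passage, with no added visits, participants, data or analyses.

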**Final Visit : Day 90**

- Client Interviews for those selected for interview
- Final Medical Assessment
- Case Report Forms (CRFs) completed by clinician which includes:
  - Final Medical Assessment
  - Patient satisfaction assessed

**Patient Follow-up**

If a participant fails to attend the scheduled weekly visit, he will be contacted by phone and/or text and will be asked to attend. The provider will make at least three attempts to contact the participant if he does not return to the study site for any study visit. Starting one day after a missed Day 7 (removal) visit, study participants will be called and texted. Study staff will attempt a home visit starting at two days post a missed visit for Day 7, removal visit. For other missed visits, only phone calls/texts will be utilized. Home visits will be used only for a missed removal visit. Participants lost to follow-up will not be replaced. All attempts to contact the client will be recorded on a contact log in the client’s file.

Patients may make unscheduled visits if they are concerned about adverse events, require review, or come in before or after a scheduled appointment. Unscheduled visit forms and adverse event review forms accommodate these possibilities.

If complications or delayed healing require longer follow-up, men will be followed by study staff as long as necessary or until study close-out. If clinical care is required after study close-out, care will be provided at the study site as part of regular clinical service. If necessary, men may be referred to a hospital near the study site for additional care.

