VMMC, PrePex™ procedure – Management of Adverse Events: The participant will be instructed to return to the study site or the nearest hospital (in the case of dislodgement or severe pain) in case of any unexpected event, for example if there is severe discoloration of the penis, signs of infection (purulence), severe or increasing pain, if any part of the device moves for any reason, if the distal part of the foreskin detaches, or any other significant concern that they may have The participant will be reminded to abstain from sex and to avoid masturbation. Clients will be instructed that if the device becomes displaced (moves) for any reason that he must seek medical care at a hospital immediately, and that if the device components become displaced and the client doesn’t return immediately for care, there is a risk of permanent damage to his penis. In the event of a complication meeting the case definition for a clinical AE associated with the VMMC, the provider will document the complication in the register according to the guidelines. Mild post-operative infections will be managed with wound cleansing and dressing, and antibiotics will be prescribed (see medications list) where clinically indicated. If device components become displaced, a surgical circumcision may be required.

Confidentiality: The following procedural efforts will be made to avoid breaches in confidentiality. All medical and programmatic data collected will be stored in a locked file cabinet, room or on password protected computers, with access provided only to authorized project staff. No one outside the investigators and team listed on the protocol or their designates will have access to the de-identified data. All investigators and analysis team members will have to sign a data use and confidentiality agreement.

3. Is it possible that you will discover a subject’s previously unknown condition (disease, suicidal intentions, genetic predisposition, etc.) as a result of study procedures?  No  Yes If yes, explain how you will handle this situation.

As a result of this study, it is possible that we will discover unknown medical conditions through our medical examination and HIV screening. However, as we are recruiting at HIV clinics, we expect all recruits to be previously diagnosed and informed of their HIV status. If any unknown condition is discovered as a result of this study, the subject will be referred for treatment and care as per Government of Zimbabwe guidelines.

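### After Day 7 the missed-visit contact is only a request to attend, so adverse events go unrecorded in men who are reached but do not come back

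*Protocol*

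**What the plan says.** The primary objective is "To assess the safety of the PrePex™ device when applied to HIV positive men by assessing the rate of the clinical adverse events". The design is single-arm: "The study will involve 400 HIV+ men". The AE rate is to be set against "the lower historical proportion of men who experience an AE with surgical MC of 2.0% as seen in Kenya".

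AE data come from visits. The Clinical Component says that "participants will be followed up over multiple review visits (Procedures and Schedule) to collect data on the clinical adverse events, pain, and time to complete" (the last item is the time to wound healing). The visit lists under Procedures and Schedule put AE occurrence on the clinician's case report form at Days 0, 7, 9 and 14 and at each later follow-up visit except Day 90. Day 90 visits are for men in the psychosocial interviews (up to 103).

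Patient Follow-up sets the response to a missed visit:
- After a missed weekly visit, "he will be contacted by phone and/or text and will be asked to attend".
- A minimum of three contact attempts applies to every missed visit.
- A missed removal visit can lead to a home visit. "For other missed visits, only phone calls/texts will be utilized".
- The attempts are kept on a contact log. Unscheduled-visit forms and AE review forms are described for men who come in.

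Care away from the study site is foreseen. In the sections on managing adverse events, participants are told to "return to the study site or the nearest hospital (in the case of dislodgement or severe pain").

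**The concern.** The only stated purpose of the contact is to get the man back to the clinic, and the only stated record is the log of attempts. If he answers but does not come, staff have been in touch with him and the file holds nothing on the primary outcome since his last visit. A man with a wound complication treated elsewhere and a man who stays away because he is well leave the same record.

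The period affected matters to the protocol's own question. Its background section reports more wound dehiscence in HIV-positive than HIV-negative men in a Ugandan surgical cohort (2.6% against 1.3%) and healing over several weeks, which is after device removal. The purpose section says that if HIV-positive men do not have higher AE rates, mandatory HIV testing may be dropped, so an undercount leans towards the conclusion that would change policy. A secondary objective is the completeness of AE reporting, which a contact without an AE question does not serve.

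**Working it through.** The protocol gives no expected loss, significance level or power, so there is no stated figure to reproduce. The check has two parts.

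**1. Which men are affected**

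| Situation after Day 7 | Is an AE since the last visit captured? |
|---|---|
| Misses a visit, attends a later scheduled one | Yes, AE item on the case report form |
| Misses a visit, comes in unscheduled | Yes, unscheduled-visit and AE review forms |
| Reached by phone or text, never returns | No, the text provides only for a request to attend |
| Not reached, never returns | No, and a phone question would not help |

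The gap that can be repaired is the third row.

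**2. How much it could matter**

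From the protocol: n = 400 and a benchmark of 2.0%. Assumed: a fraction d is never seen again, men who are seen have an AE rate of 2.0%, and the unseen men have k × 2.0% after their last visit.

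- Expected events at the benchmark: 400 × 0.02 = 8. The exact 95% interval for 8/400 is 0.87% to 3.90%.
- Recorded events: 400 × (1 − d) × 0.02
- Missed events: 400 × d × 0.02 × k
- True rate: (recorded + missed) / 400

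With d = 10%, 40 men are unseen and 360 × 0.02 = 7.2 events are recorded, which is 1.8% of 400 or 2.0% of 360.

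| k | Missed events | True rate |
|---|---|---|
| 1 | 40 × 0.02 = 0.8 | 8.0/400 = 2.0% |
| 3 | 40 × 0.06 = 2.4 | 9.6/400 = 2.4% |
| 5 | 40 × 0.10 = 4.0 | 11.2/400 = 2.8% |

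Over d = 5% to 20% and k = 1 to 5, missed events run from 20 × 0.02 = 0.4 to 80 × 0.10 = 8.0.

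Two readings follow. The count over all 400 men can only be too low. The rate among men seen is unbiased when k = 1, and would be too high if the unseen men had fewer events (k below 1), for example because they had healed.

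With no information on the 40 men and 7 events observed, the bounds are 7/400 = 1.75% and (7 + 40)/400 = 11.75%.

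**The case against.** The strongest reply is that this is a narrow gap. AEs are asked about at every scheduled visit through at least Day 49, so one missed visit is usually made good at the next. Unscheduled visits have their own forms, men with complications are followed for as long as needed or until study close-out, and men receive about US$6 per visit. AEs must meet a case definition, which favours examination by a clinician, so asking the man to attend is a sensible first response. The standard operating procedures and case report forms (Appendices 3 to 5) are not at hand and could contain a phone query. All of this stands, and it confines the point to men who do not return.

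Three stronger readings are tempting and are not supported:
- A reader might infer that staff speak to each such man three times. The text requires at least three attempts, by phone and/or text, not completed calls.
- A reader might infer that non-returners are the men most likely to have been treated elsewhere. The nearest-hospital instruction names only dislodgement and severe pain, and dislodgement belongs mainly to the device-wearing period before Day 7. Non-returners may equally be healed.
- A reader might take 10% loss as the expected figure, since the background reports over 90% attendance at 4 to 6 weeks in the Ugandan cohort. That is one visit in a surgical study and does not show that 10% here would miss every later visit.

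The objection does not remove the third row of the first table. What is not asked during the contact cannot be recovered later by any analysis.

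**Conclusion.** The point holds for men who are reached after a missed visit and do not return. For them the protocol text provides no record of AEs or outside care since the last attended visit, and the AE count set against the 2.0% benchmark can only be lowered by this. The size is unknown because the protocol gives no expected number of non-returners. About 0.8 to 4 missed events against about 8 expected is an illustration that rests on an assumed 10% loss and an assumed AE rate of 1 to 5 times 2.0%. It does not show that the reported rate will be biased: if loss is unrelated to AEs, the rate among men seen is not. The conclusion also depends on Appendix 3 not already containing such a query. The change is worth making because so few events are expected and the contact is already required.

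**What to change.** Amend Patient Follow-up so that, when a man is reached after a missed visit, staff:
- ask a short fixed list: bleeding, infection, wound opening or any other problem since the last visit, and whether care was sought elsewhere and where;
- enter the answers on the existing AE review form;
- still ask him to attend.

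Report the AE rate with clinic-confirmed events as primary, and again with phone-reported events added. State how many men had no later contact. Do not use phone answers to certify healing. If Appendix 3 already contains such a query, a reference to it in Patient Follow-up is enough.

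The cost is a few minutes per contact, with no new visits or staff. Written consent to phone contact is already sought, and the Data Collection table already lists interview as the method for safety data. The downsides are that phone reports are not examined, which is why they are shown separately, and that men who are not reached remain unobserved.
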